**Methods:**

A single-center, randomized controlled trial of pediatric patients with acute lung injury after surgery for congenital heart disease who will receive prone position ventilation or usual care (control group). A total of 68 children will be enrolled according to the inclusion criteria. The main outcome measures will be lung compliance and oxygenation index. The secondary outcomes will be duration of mechanical ventilation, length of stay in cardiac intensive care unit, reintubation rate, and complication rate.

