### Intervention strategies

The family members of the subjects will be informed about the purpose and methods of prone position ventilation, and their consent will be obtained for participation in the study.Careful assessment of the disease status will be performed and adequate fixation of the various cannulas and vascular catheters will be ensured.Enteral nutrition will be suspended 30 min before and the gastrointestinal nutrition tube will be closed before preparing for prone positioning.The timing of start of prone position ventilation will be determined by a team of medical personnel after determining the following: (1) the child has a stable circulation and shows no restlessness, and (2) the routine medical care has been provided.The child will be placed in the prone position with the participation of researchers, doctors, and the nursing staff. The child’s head will be tilted to one side to avoid damage to the eyes and nose due to compression; the arms will be bent upwards and placed on both sides of the head in a W-shaped configuration. The arms can also be placed in another position depending on the specific situation. Both lower limbs will be bent downwards to form an “M” shape; soft pillows will be used below both knee joints to avoid compression.Meticulous care will be exercised to ensure smooth fixation of mechanical ventilation, endotracheal tube, and various catheters.The depth of sedation will be calibrated during the entire prone position ventilation period to achieve good man-machine synchronization.Requirements during prone position ventilation: (1) adequate suction of the sputum and (2) the mechanical ventilation tube is suspended in the air, and the head is in left or right side position for 1–2 h.In a crossover design, the prone position will be maintained for 6–8 h per day until the improvement in oxygenation index (mean airway pressure × FIO_2_ × 100)/PaO_2_). Oxygenation index exceeding the baseline value or chest X-ray or CT findings suggest lung tissue recruitment. Prone position will be discontinued in case of deterioration of the condition (such as development of hemodynamic instability, pneumothorax, mediastinal emphysema, catheter loss, facial trauma, or formation of pressure ulcer).

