## Outcomes

### Outcomes (effectiveness)

Main outcome indicators: lung compliance, SPO_2_, respiratory rate, peak, positive end-expiratory pressure (PEEP); laboratory indices: oxygenation index (mean airway pressure × FIO_2_ × 100)/PaO_2_), oxygen partial pressure (PaO_2_), carbon dioxide partial pressure (PaCO_2_), pH; chest radiograph.Secondary outcome indicators: (1) duration of mechanical ventilation; (2) length of stay in cardiac intensive care unit (CICU); (3) incidence of reintubation; (4) incidence of complications: pressure skin injury, slippage of the intubation, compression, and displacement of the pipeline; (5) hemodynamic stability: heart rate (HR), invasive arterial blood pressure (ABP), central venous pressure (CVP).

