### Statistical analyses

The SPSS 23.0 statistical software will be used for statistical analyses. Quantitative variables conforming to normal distribution will be presented as mean ± standard deviation. Between-group differences will be assessed using the *t* test (paired *t* test before and after prone position, hemodynamic indicators, oxygenation indices, etc., will be assessed using group *t* test). Non-normally distributed quantitative variables will be presented as Chinese numbers (quartiles), and non-parametric tests will be used to assess between-group differences. Categorical variables will be presented as frequency and percentage, and between-group differences will be assessed using chi-squared test or Fisher exact test.

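### PEEP, respiratory rate, peak pressure and uncorrected blood-gas values are listed as main effectiveness outcomes, although in ventilated infants they are set by staff or depend on the support given; the abstract's shorter list avoids this

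*Protocol article*

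**What the plan says.** Under Outcomes (effectiveness), the protocol article opens its list of main indicators with lung compliance and SpO2, followed by "respiratory rate, peak, positive end-expiratory pressure (PEEP". It continues with laboratory indices: the "oxygenation index (mean airway pressure × FIO_2_ × 100)/PaO_2", then "oxygen partial pressure (PaO_2_), carbon dioxide partial pressure (PaCO_2_), pH; chest radiograph". All of these are main indicators, and none is ranked above another.

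The Methods paragraph of the abstract is narrower: "The main outcome measures will be lung compliance and oxygenation index". The sample size is also built on a quantity called oxygenation index.

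Invasive ventilation is an inclusion criterion, so every infant has ventilator settings chosen by staff. Statistical analyses mentions a paired t test before and after proning and then says that "hemodynamic indicators, oxygenation indices, etc., will be assessed using group" t tests. It mentions no account of FiO2, airway pressure or set rate. Intervention strategies says, for the prone procedure, "The depth of sedation will be calibrated during the entire prone position ventilation period to achieve good man-machine synchronization". No matching sentence describes sedation in the control arm.

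**The concern.** An effectiveness outcome should respond to the treatment through the process the trial is studying, here the function of the lung. The variables in the Outcomes list fall into three groups.

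- **Settings.** PEEP is chosen by staff. Respiratory rate in a ventilated infant is wholly or partly chosen, and any remainder depends on sedation. Neither has a clear direction of benefit: a lower PEEP may reflect weaning, or simply less recruitment pressure.
- **Responses that depend on support.** PaO2, SpO2, PaCO2 and pH depend on the FiO2, pressure and rate in use. Peak pressure is a setting or a response depending on ventilator mode.
- **Measures less exposed to this.** The oxygenation index carries FiO2 and mean airway pressure with PaO2. Lung compliance is the other.

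If the whole list is tested as main outcomes, two misreadings are possible. If support is reduced as the lung improves, similar PaO2 and SpO2 in the two arms may be read as no effect on gas exchange. A difference in PEEP or rate that arises from staff choices may be read as a benefit of position. Either could sit beside a contrary oxygenation index, and the plan does not say which result governs.

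**Working it through.** **1. The plan's own effect size.** From Sample size/power calculation: means 276 and 228, SDs 68 and 67.
- Pooled SD = √((68² + 67²)/2) = 67.5; d = 48/67.5 = 0.711. The plan states 0.71.
- Normal approximation, two-sided 0.05 (assumed; sidedness is not stated), power 0.80: n = 2(1.96 + 0.8416)²/0.711² = 31.05 per arm; × 1.1 = 34.15. The plan states 34.

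The stated figures reproduce to rounding. I use 0.71 below only as a convenient effect size. The planning means do not fit the printed index formula: lower is better by that formula and the inclusion threshold is 4, yet the planning values are in the hundreds and higher in the experimental arm.

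**2. PaO2 with and without the support given.** Index = mean airway pressure × FiO2 × 100 / PaO2. Illustrative inputs (mine): mean airway pressure 10, PaO2 70.
- FiO2 0.6: 10 × 0.6 × 100 / 70 = 8.6
- FiO2 0.4: 10 × 0.4 × 100 / 70 = 5.7

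The index falls by one third (1 − 0.4/0.6) while PaO2 does not move. A comparison of PaO2 alone records nothing.

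**3. What partial titration would do to a test of raw PaO2.** Assumptions, none from the article: lung efficiency on the log scale has SD 0.27 and differs between arms by 0.71 SD; FiO2 absorbs a fraction k of it; PaO2 carries the rest plus noise of SD s = 0.10 or 0.15.
- Arm difference in log PaO2 = (1 − k) × 0.71 × 0.27
- SD of log PaO2 = √([(1 − k) × 0.27]² + s²)
- At k = 0.5, s = 0.10: 0.0959/0.168 = 0.57 SD.

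Two-sided t-test power, 34 per arm:

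| k | s = 0.10 | s = 0.15 |
|---|---|---|
| 0 | 77% | 71% |
| 0.5 | 64% | 49% |
| 0.75 | 36% | 22% |
| 0.9 | 12% | 8% |
| 1 | 5% | 5% |

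A 4,000-run simulation of the same model agrees (71–79% at k = 0). In this model PaO2/FiO2 recovers the full efficiency whatever k is, so its power stays at the k = 0 row. Since 34 already includes 10% attrition, about 31 per arm (34 × 0.9 = 30.6) may be analysed; the k = 0 row is then 73% and 67%, and full titration still gives 5%.

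**4. The opposite error.** Suppose position has no lung effect but a staff-set variable differs between arms by an assumed 0.2, 0.3 or 0.5 SD. With 31 per arm the t test is significant in 12%, 21% or 49% of trials. The test correctly detects a difference in settings; the error lies in calling it effectiveness.

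**5. The two lists side by side.** The abstract's two main outcomes are the two less exposed to these problems. Every variable in question appears only in the longer list.

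**The case against.** The strongest reply is that the conclusion will rest on lung compliance and the oxygenation index: the abstract names only these, the trial is sized on a quantity given the index's name, and readers will see PaO2 beside them. That limits the damage, and it means the defect does not reach every main outcome. It does not remove it, because the Outcomes section still gives the other variables the same rank.

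Second, the article gives no FiO2 rule, no SpO2 target and no account of settings at sampling. The full protocol may standardise them, and a condensed article may leave that out. This stands for the gas values. It does not rescue PEEP or a set rate: no measurement rule makes a setting a measure of the lung.

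Third, the power figures depend on the model. If titration instead removes a fraction of a 0.71 SD effect while the SD stays fixed, power with 31 per arm is 28% at one half and 11% at three quarters, well below the table. The endpoints are informative; the values between are illustrations.

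Three stronger readings are tempting, and the documents support none of them.
- That these variables reflect only staff action. This is too strong for PaO2, SpO2, PaCO2, pH and peak pressure: under partial titration raw PaO2 still carries part of the lung effect. The oxygenation index is not free of staff influence either, since it contains mean airway pressure.
- That sedation differs between the arms. The sedation sentence belongs to a description of the prone procedure, usual care is not detailed, and Background mentions sedative muscle relaxants during supine ventilation. A difference is a risk, not a stated fact.
- That every listed variable will be compared raw by the group t test. Statistical analyses names haemodynamic indicators and oxygenation indices and ends in an open-ended phrase; application to the rest is an inference. The paired test would not help, because settings can also change between the two time points.

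**Conclusion.** The point holds in a limited form. For PEEP and a set respiratory rate it follows from what the variables are and needs no assumption about practice: an arm difference is not evidence of a lung effect. For PaO2, SpO2, PaCO2, pH and, depending on mode, peak pressure, it is conditional: compared alone, they can understate a lung effect if support is reduced as the lung improves. The size of that loss cannot be derived from the article; it runs from none with no titration to complete with full titration. Lung compliance and the oxygenation index are less exposed, so this is a correction that should be made to the outcome list, not a reason to discount the trial's main comparison.

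**What to change.** Align Outcomes (effectiveness) with the abstract:

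- Keep lung compliance and the oxygenation index, by the printed formula, as the main outcomes, and reconcile the planning means and SDs in the sample-size section with that formula.
- Report PEEP, peak pressure, respiratory rate, FiO2 and sedation by arm as descriptive co-intervention data.
- Move PaO2, SpO2, PaCO2 and pH to supportive outcomes. Express PaO2 and SpO2 relative to FiO2 and mean airway pressure at the same time point. State in Statistical analyses that no effectiveness claim will rest on the raw values.

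FiO2, mean airway pressure and PaO2 are already needed for the index, so the outcome changes are a matter of wording and alter no clinical rule. The sample-size values need a check against the pilot data. The small cost is fewer variables on which an effect can be claimed.

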**Table Taba:** 

Inclusion criteria	Exclusion criteria
**- Pediatric patients with lung injury after** surgery for **congenital heart disease or** those in whom **chest X-ray** and **CT** findings indicate the need for augmenting pulmonary drainage due to **pulmonary complications**.	-Hemodynamic instability, severe hypotension, ventricular arrhythmia - Pacemaker dependent - ECMO
**- Invasive mechanical ventilation**	-Intracranial hypertension
**-**Age range: **0–12 months**	-Active acute bleeding
**-Stable hemodynamics, more than 72 h after surgery**	-Spinal injuries and untreated unstable fractures, orthopedic surgery or recent abdominal surgery
**-Informed consent of family members**	-Facial trauma
	Severe pneumothorax
	-Patients with delayed chest closure and wound infection requiring immobilization

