### Sample size/power calculation

According to pre-experimental investigations, the average oxygenation index required by the experimental group of children is 276, with a standard deviation of 68, and the control group has an average oxygenation index of 228, with a standard deviation of 67. Comparing the two independent sample means, *α* = 0.05, *β* = 0.2, the Gpower sample calculation software showed an effect size of 0.71. The ratio of the test group and the control group is 1:1. An attrition rate of 10% has been factored in the sample size calculation. The calculated sample size is 34 patients per group and total sample size is 68 patients.

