## Discussion

The purpose of our study was to investigate the feasibility and clinical effectiveness and of prone ventilation in children with ALI after surgery for congenital heart disease in improving oxygenation status. Our findings may help improve the lung protection of critically ill children with congenital heart disease, reduce the duration of mechanical ventilation, and shorten their stay in the CICU. Since this study was conducted for the first time in a single center, there are some deficiencies in the design and content of the study. It is hoped that there will be more in-depth studies on protective lung ventilation in children with congenital heart disease in the future. The results of our study may provide standards for the development of prone position ventilation for children with congenital heart disease. At the same time, we also hope to establish a joint medical-care evaluation mechanism to provide guidance for diagnosis and treatment.

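### Ventilation duration and CICU stay have no stated time origin although entry is open-ended beyond 72 h, so on their ordinary reading they take in variable pre-randomisation time

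*Protocol article*

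**What the plan says.** All of this is in the protocol article.

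- **Outcomes (effectiveness)** names the first two secondary indicators as "1) duration of mechanical ventilation; (2) length of stay in cardiac intensive care unit (CICU". It gives no start or end point for either.
- **Inclusion and exclusion criteria**, in the list and in the table, require "Stable hemodynamics, more than 72 h after surgery" and "Invasive mechanical ventilation". Neither place gives a latest time of entry.
- **Intervention strategies** leaves the start of treatment open as well: "The timing of start of prone position ventilation will be determined by a team of medical personnel".
- **Statistical analyses** plans a t test or a non-parametric test between groups for quantitative variables. No adjustment for time since surgery is mentioned.
- **Block randomization** uses blocks of 4 without stratification by postoperative day.
- **Discussion** hopes that the findings will help to "reduce the duration of mechanical ventilation, and shorten their stay in the CICU", so these two outcomes carry the clinical-benefit message although they are secondary.

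**The concern.** An infant who meets the criteria is already on the ventilator when allocated, and has normally been in the CICU since surgery. One infant may enter on day 4 and another some weeks later. If each duration runs from intubation or from CICU admission, it is the sum of a part before allocation, which treatment cannot affect, and a part after it, which treatment may shorten. The first part varies between infants because the entry window has no upper end.

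The stake is precision. The comparison carries extra variance, and with 34 per arm a few late entrants falling by chance into one arm can blur or exaggerate a difference in means. A relative effect (percentage reduction) would also be diluted, because untreatable days enlarge the denominator.

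**Working it through.** **Is there a plan figure to reproduce?** Not for these outcomes: the article states no mean, SD or target difference for ventilation duration or CICU stay. Its only sizing figures, under Sample size/power calculation, concern the oxygenation index: mean 276 (SD 68) with prone ventilation against 228 (SD 67) in controls. The pooled SD is √((68² + 67²)/2) = 67.5, and d = (276 − 228)/67.5 = 0.711, which agrees with the stated 0.71. I borrow d = 0.71 below only as a convenient effect size. It says nothing about ventilation days.

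**Step 1: split the outcome.** Write T = W + D, where W is time before randomisation and D is time after it.

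- Difference in means: E(T | prone) − E(T | control) = E(D | prone) − E(D | control), because randomisation makes E(W) the same in both arms. There is no bias.
- If W were exactly 72 h for everyone, Var(T) = Var(D), so the standard error would also be unchanged. Only variation in W matters.

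**Step 2: variance.** Let r = SD(W)/SD(D) and let ρ be the correlation of W and D. Then Var(T)/Var(D) = 1 + r² + 2ρr, which is 1 + r² when ρ = 0.

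**Step 3: chance imbalance.** With 34 per arm, the between-arm difference in mean W has standard error SD(W) × √(2/34) = 0.243 × SD(W).

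**Step 4: illustration.** Assumptions: 34 per arm, two-sided α = 0.05, two-sample t test (noncentral t), and a true effect of 0.71 SD on the post-randomisation scale. Counting W shrinks the standardised effect to 0.71/√(variance ratio).

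| r | Variance ratio, ρ = 0 | Equivalent n per arm (34 / ratio) | Power, ρ = 0 | Power, ρ = 0.3 |
|---|---|---|---|---|
| 0 (clock starts at randomisation) | 1.00 | 34.0 | 0.82 | 0.82 |
| 0.25 | 1.06 | 32.0 | 0.80 | 0.75 |
| 0.33 | 1.11 | 30.6 | 0.78 | 0.71 |
| 0.5 | 1.25 | 27.2 | 0.73 | 0.64 |
| 0.67 | 1.44 | 23.5 | 0.67 | 0.57 |
| 1.0 | 2.00 | 17.0 | 0.53 | 0.43 |

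Rows 0.33 and 0.67 use r = 1/3 and 2/3. They correspond, for example, to an assumed SD of 6 days after randomisation with an SD of 2 or 4 days before it.

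**Step 5: direction of the dependence.** Late entrants may well be sicker and stay longer afterwards (ρ > 0), which makes the loss larger. If instead ρ were below −r/2, the sum would vary less than D alone and the loss would vanish. The documents do not settle the sign.

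**The case against.** **The article does not say that whole durations are used.** A reader might infer that the plan fixes total ventilation time and total CICU stay as the outcomes. It does not: it names them and is silent on the origin. This is a condensed article, and a full protocol or SAP that is not shown may start both clocks at randomisation. That objection stands against any claim that pre-randomisation days are in fact counted. It does not dispose of the point. The article combines an unbounded entry window, ventilation as an entry condition, unqualified duration terms and an unadjusted test, and anyone following that text in the ordinary sense of the terms would count time before allocation.

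**At least three days are not assured.** A reader might infer that every infant brings three or more ventilated days into the outcome. The criteria require ventilation at entry, not continuous ventilation since surgery. A reintubated infant would qualify, and the current episode could be short. A shared 72 h would cancel in any case.

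**There is no bias.** A reader might infer a distorted treatment effect. Allocation is randomised, so the absolute mean difference is unbiased and only precision suffers.

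**The magnitude is assumed.** This stands. SDs, correlation and effect size are not in the documents, and the trial was not sized on these outcomes, so no planned power is lost. At r = 0.25 with independence the loss is about two percentage points.

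**The planned test may be rank-based.** Durations are usually skewed, and the article assigns non-parametric tests to non-normal variables. Ranks limit the pull of one or two extreme stays, so the chance-imbalance worry is weaker there. They do not remove the noise that variable entry times add to the ranking.

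**Conclusion.** The point holds as a weakness of definition with a cost in precision. Entry time varies without an upper limit, infants are already ventilated when allocated, and the two durations have no origin. On their ordinary reading they include variable pre-randomisation time that the planned tests leave in.

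The size cannot be computed from the documents. Under independence the variance grows by 1 + r²: 11% at r = 0.33, 44% at r = 0.67, and a doubling only if entry times vary as much as the later course. A positive correlation makes it worse, and a sufficiently negative one removes it.

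The main outcomes, the stated sample size and the validity of the randomised comparison are untouched. This is worth correcting because it is cheap and because the Discussion rests its hoped-for clinical benefit on these two outcomes.

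**What to change.** 1. Define both outcomes from randomisation: days of invasive ventilation from randomisation, and CICU days from randomisation. Randomisation is the only origin both arms share: the first prone session does not exist for controls, and its timing is a team decision after allocation.
2. Report total ventilation time and total CICU stay descriptively, by arm.
3. Adjust both comparisons for days from surgery to randomisation, a pre-allocation variable. Where ventilation has been continuous since surgery, this adjustment in a linear model gives the same treatment estimate whether the outcome is total or post-randomisation days, so it also protects against ambiguity in the origin.
4. If a full protocol or SAP already starts the clocks at randomisation, say so in the outcome definition. Trial status reports follow-up as ongoing, so settle the wording before any comparison by group.

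The cost is one line of outcome wording and one covariate. It needs no extra infants, visits or procedures, assuming that dates of surgery, randomisation, extubation and CICU discharge are available from the clinical record. The article does not list the dates collected.

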With the advances in cardiac diagnosis and treatment technology, patients undergoing treatment of congenital heart disease tend to be younger and have lower body weight. Maintenance of the respiratory function after cardiac surgery in infants and young children is a key determinant of successful surgical outcomes. Owing to the complexity of cardiac surgery and the prolonged operative time, cardiac surgery is performed under low temperature cardiopulmonary bypass; this increases the risk of hypoxemia after cardiopulmonary bypass. In infants and young children, use of cardiopulmonary bypass increases the pulmonary blood flow and reduces lung tissue compliance. High concentration of oxygen in the medium and the impaired thoracic integrity caused by the surgical incision can easily lead to postoperative hypoxemia [11]. Different degrees of lung injury may occur after cardiac surgery. In our department, the incidence of postoperative pulmonary complications is 11.3%, of which the incidence of atelectasis, VAP, and lung consolidation is 8.2%, 1.4%, and 0.80 %, respectively. Delay in the correction of hypoxemia and lung injury in children may lead to adverse life-threatening outcomes. In such settings, early mechanical ventilation in the prone position can improve the blood oxygen content and alleviate ventilator-related lung injury. At the same time, timely and effective respiratory management and lung physical therapy can be performed to correct hypoxemia. Increase in the partial pressure of blood oxygen can reduce complications and facilitate weaning of the patient from the ventilator. Due to the safety of cardiac surgery, only a few studies [12] have investigated the effect of prone position ventilation for patients with hypoxia after cardiac surgery.

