### Quality control

The randomization method will be strictly implemented. In the event that the intervention cannot be implemented due to severe intolerance to prone position ventilation or rapid deterioration in a patient’s condition, these patients will be included in the “intention to treat” analysis. All nurses participating in the study intervention will be meticulously trained in order to ensure standardization of the study procedures and data collection. To ensure consistency of data collection, spot checks will be performed to assess the quality of data collected and to take corrective actions to prevent recurrence of errors or omissions.

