### Assessment of risks and benefits

All subjects will be closely monitored for adverse events. The incidence of pressure ulcers, wound infection, unplanned rechecks, and catheter slippage will be recorded. These data will be published along with the main results of the study. Personal and telephonic meetings will be regularly conducted to ensure close coordination between the research teams.

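### Ventilation duration and CICU stay are compared as raw durations with death in no outcome list, so a mortality difference between arms can distort both, in a direction set by when deaths occur

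*Protocol article*

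**What the plan says.** The protocol article, under Outcomes (effectiveness), opens its secondary outcomes with "1) duration of mechanical ventilation; (2) length of stay in cardiac intensive care unit (CICU". It continues with "3) incidence of reintubation; (4) incidence of complications: pressure skin injury, slippage of the intubation, compression, and displacement of the pipeline" and then hemodynamic measures. Death is not in this list, in the main outcomes, or in the abstract's outcomes. Under Assessment of risks and benefits, the events named for recording are these: "The incidence of pressure ulcers, wound infection, unplanned rechecks, and catheter slippage will be recorded". Death is not named there either.

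The Statistical analyses section treats all quantitative variables alike. For normally distributed ones, "Between-group differences will be assessed using the *t* test"; for the rest, "non-parametric tests will be used to assess between-group differences". It does not say which non-parametric test, or how a duration that ends in death enters it.

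Under Quality control, infants in whom prone positioning cannot be carried out because of intolerance or rapid deterioration are kept: "these patients will be included in the “intention to treat” analysis".

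**The concern.** Ventilation and CICU stay can end in two opposite ways: recovery (extubation, discharge) or death. A raw duration does not tell them apart. Taken at face value, an infant who dies on day 2 contributes 2 days and ranks ahead of a survivor extubated on day 7. An infant who dies after a long course contributes a long duration. If mortality differs between arms, the comparison therefore mixes the effect on recovery with the number and timing of deaths.

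The Background and Discussion name shorter ventilation as a hoped-for benefit, and the Discussion adds shorter CICU stay. These two results are therefore likely to be read as evidence of patient benefit. With no mortality outcome beside them, a reader could not judge how far deaths had shaped them.

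**Working it through.** **Figures in the plan.** The article gives no mortality rate and no expected duration, so there is no stated figure to reproduce. The only input taken from it is 34 infants per group (Sample size/power calculation).

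**Assumptions.**
- Survivors' duration is lognormal with median 7 days and log SD 0.7, the same in both arms (no treatment effect in survivors).
- Mortality is 15% prone v 5% control, that is 0.15 × 34 = 5.1 and 0.05 × 34 = 1.7 expected deaths.
- Time of death is uniform over a stated window. For an infant who dies, the duration is the time to death.
- The test is a two-sided 5% Mann-Whitney test, over 4,000 simulated trials per scenario.

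**Shift in the mean.** With no effect in survivors, the expected difference (prone minus control) is

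(mortality prone − mortality control) × (mean time to death − mean survivor duration).

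Mean survivor duration = 7 × exp(0.7²/2) = 7 × exp(0.245) = 8.94 days. The excess mortality is 0.15 − 0.05 = 0.10.

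| Deaths on days | Mean time to death | Expected shift (days) | Simulated shift | Significant, favouring prone (nominal 2.5%) |
|---|---|---|---|---|
| 1–4 | 2.5 | 0.10 × (2.5 − 8.94) = −0.64 | about −0.7 | about 8–9% |
| 2–14 | 8.0 | 0.10 × (8.0 − 8.94) = −0.09 | about −0.1 | about 2.5% |
| 5–20 | 12.5 | 0.10 × (12.5 − 8.94) = +0.36 | about +0.3 | about 1% |
| 3–28 | 15.5 | 0.10 × (15.5 − 8.94) = +0.66 | about +0.6 | about 1% |

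The sign changes where mean time to death equals mean survivor duration, here about 9 days.

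**Other mortality patterns, deaths on days 1–4.**
- 5% v 5%: no shift, and 2.0% of trials significantly favour prone.
- 20% v 5%: 0.98 days shorter, and 14.5% favour prone.
- 5% v 15% (prone prevents deaths): prone looks 0.63 days longer.

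**Sensitivity to the model of death.** A second model lets death only cut short the duration the infant would otherwise have had (log SD 0.6). At 15% v 5%, the shift is −0.59 days for deaths on days 1–4 and −0.12 days for days 5–20. The early-death result barely changes. The late-death shift becomes small and no longer goes against the higher-mortality arm.

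**Effect of the remedy.** With death scored as zero ventilator-free days, at 15% v 5% and deaths on days 1–4, the rate of significant results favouring prone falls to 0.5%.

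**The case against.** **The text sets no rule for deaths.** A reader might infer that the protocol scores an early death as a short, favourable duration. It does not say so. It names two durations and gives general tests; whether infants who die are truncated, excluded or ranked worst is left open. A condensed article may leave that convention to a fuller document, and ranking death worst would itself be a non-parametric test. This limits the point to what follows if the published text is applied as it stands. It does not remove it: the published outcomes are raw durations, and the published outcome and event lists leave out death.

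**Timing decides the direction.** A reader might infer that the arm with more deaths always looks better. The table shows otherwise: with later deaths the shift disappears or goes the other way. This objection stands in full.

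**The adverse scenario may be unlikely.** Eligibility requires stable hemodynamics more than 72 h after surgery and excludes infants on ECMO or with active acute bleeding. Nothing in the article supports 15–20% mortality within four days, concentrated in one arm. This also stands; the scenario is an illustration.

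**Supporting passages should not be stretched.** The Background says "Delay in the correction of hypoxemia and lung injury in children may lead to adverse life-threatening outcomes". That concerns delayed treatment and gives no death rate. The Quality control sentence, which begins "In the event that the intervention cannot be implemented due to severe intolerance to prone position ventilation or rapid deterioration", does not mention death. It shows only that infants who deteriorate remain in the analysis. Nor can one conclude that deaths would go unnoticed, since all subjects are to be monitored for adverse events. What can be said is that mortality by arm is not a listed outcome.

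**Conclusion.** The point holds in a limited form. As published, the two duration outcomes do not separate recovery from death, and mortality is not listed beside them. A between-arm difference in mortality can therefore distort both comparisons.

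Under the stated assumptions at 15% v 5% mortality, the distortion runs from about 0.7 days in favour of the higher-mortality arm (deaths on days 1–4) to about 0.6 days against it (deaths on days 3–28). It is close to zero for deaths on days 2–14, and absent when mortality is equal. The documents fix neither the mortality nor its timing, so neither the size nor the direction can be predicted for this trial.

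A reader might go further and infer that the trial's result will be reversed or that its main conclusion is unsafe. The documents do not support that. These are secondary outcomes; the abstract's main outcomes are lung compliance and oxygenation index, and the sample size rests on oxygenation index. This is a cheap improvement to the secondary outcomes.

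**What to change.** - Count ventilation duration and CICU stay from randomisation in both arms.
- In the between-arm rank test, rank death before extubation (or before CICU discharge) as the worst outcome. Alternatively, use ventilator-free and CICU-free days to a fixed day, for example day 28, with death scored as zero.
- Add all-cause mortality by arm to the outcome list.
- Report raw durations in survivors as description only, because survivors are selected after randomisation.

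The cost is protocol wording and use of the dates of extubation, CICU discharge and death, which should already be in the clinical record. No extra infants are needed. The downside is that the new measure mixes death with duration, so both components must be shown next to it.
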